### Sample size calculations

Household sample size calculations are based on an endline comparison of two groups (intervention versus control), using the proportion of women giving birth in a health facility as the primary outcome. On the basis of an observed institutional delivery rate of 50 % at baseline [10] and an assumed coefficient of variation of 0.2, a sample size of 60 intervention and 60 control clusters with a total of 20 women in each cluster are estimated to provide 80 % power to detect an 8 percentage point increase in the rate of institutional deliveries in the intervention group compared with the control at 5 % level of significance. Assuming a coefficient of variation of 0.1 reduces the detectable difference to 6 percentage points. It is anticipated that the study will have power to detect smaller differences once the analysis controls for covariates and utilises data from two survey rounds.

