### Empirical analysis

The impact evaluation relies primarily on the household data. We use a difference-in-difference strategy to estimate impacts [34]. This involves a comparison of changes in the outcomes over time between the intervention and the comparison groups. The analysis exploits the longitudinal nature of the data generated by the recall period used in the two rounds of the household survey and information on the precise timing of the introduction of social franchising in each study area. Specifically, using individual level data, we regress each outcome on a dummy variable indicating whether social franchising has been introduced in the area at the time of birth, area fixed effects and quarter year fixed effects. Unadjusted estimates are reported as well as those that adjust for household characteristics. Controls for household characteristics include below the poverty line status, urban residence, religion, ethnicity, maternal education, parity, multiple birth and the recall period. We cluster the standard errors at the area level.

We test whether the social franchising model has an effect in two ways: the first analysis compares intervention areas with the two sets of comparison areas pooled together, and the second analysis compares the intervention areas with the comparison areas in adjoining districts without social franchising. The latter may arguably be less prone to selection bias since comparison areas in neighbouring districts are beyond the geographical reach of the project and may offer a more credible counterfactual. If the social franchising model is found to have an effect on any of the main outcomes, we conduct subgroup analyses with respect to below the poverty line status, maternal education and caste. Finally, to assess the so-called parallel trends assumption that underpins the difference-in-difference approach, we exploit the recall period in the household data to verify that trends in each of the outcomes are similar between the three study arms before the introduction of the social franchising model. Evidence of diverging pre-trends would be a cause for concern. Baseline outcomes and characteristics of women are also summarised for each study arm with continuous variables presented as mean (standard deviation) and categorical variables by frequencies (percentage). An additional file describes the empirical strategy of the impact evaluation in further detail [see Additional file 4].

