The presence of multiple outcomes leads to the risk of arbitrarily selecting statistically significant outcomes where high values of test statistics arise by chance. Testing each hypothesis one at a time with a fixed significance increases the probability of a type-I error exponentially as the number of outcomes tested grows. We deal with multiple outcomes using several procedures that are implemented for conceptually similar groups of outcomes listed in Tables 2, 3 and 4 [35, 36]. First, we present standardised treatment effects by creating an index for multiple outcomes within each domain and testing for an effect on the index. Implicitly, this weighs each outcome the same within a domain. Second, we present family-wise *p* values adjusted to account for the multiple outcomes within a domain using the free step-down resampling method of Westfall and Young [37].

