## Discussion

The social franchising model in Uttar Pradesh seeks to increase access to and use of basic obstetric care, emergency obstetric care and family planning services. The approach is novel in its focus on maternal health services, its effort to engage with low level and, in some cases, informal healthcare providers and its use of technology such as telemedicine. Whether such an approach to social franchising represents the way forward to improving utilisation and quality of maternal health services is unclear. The evaluation of this model will thus provide an important contribution to the existing literature.

The study’s contribution to knowledge will be strengthened by certain attributes of the study design. The matched difference-in-difference approach provides better causal inference than that obtained in previous studies of social franchising which have rarely used control groups. The large number of outcomes gives us the opportunity to capture the full range of effects across the continuum of care generated by this multifaceted health system intervention. By accounting for multiple inferences, we deal with the risk of specifying many outcomes. Finally, we complement the impact evaluation with a cost-effectiveness analysis and an examination of the implementation process to understand how the programme worked or failed to work and its potential for scaleup.

The findings will need to be interpreted with several potential limitations in mind. First, we must rely on women to recall delivery care practices during childbirth to come to conclusions as to the impact of the social franchising model on quality of care. Measures of quality that use standardised patients are the gold standard but cannot be used in the case of childbirth [26, 49]. Second, we anticipate issues to do with recall. Some indicators place a heavy burden on the woman’s ability to recollect events up to 2 years ago and are therefore likely to suffer from recall problems. In our adjusted estimates of impact, we control for the recall period and the issue is only a concern for the evaluation insofar as recall bias differs between study arms. Third, we note the potential for bias in our impact estimates given that the offer to join the social franchise network is not randomised. To attempt to limit selection problems, we use matched control areas to provide a credible a counterfactual as possible.

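### Multiplicity control stops at the edge of each of 14 domains, neither of two contrasts is primary, and facility birth has no primary test, so the Discussion overstates the protection

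*Protocol article*

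**What the plan says.** All references are to the protocol article.

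- **Procedures (Empirical analysis).** Two are given. An index is formed and tested for each domain, and family-wise p values are "adjusted to account for the multiple outcomes within a domain using the free step-down resampling method" of Westfall and Young. Both operate inside one domain.
- **Contrasts (same section).** The effect is tested twice: intervention areas (Group A) against both comparison groups pooled (B and C), and Group A against Group C alone. The second is described as arguably less exposed to selection bias, but neither is made primary.
- **Subgroups (same section).** "If the social franchising model is found to have an effect on any of the main outcomes, we conduct subgroup analyses". The term *main outcomes* is not defined, and the text does not say whether adjusted or unadjusted results count.
- **Primary outcome (Sample size calculations).** The calculation is made "using the proportion of women giving birth in a health facility as the primary outcome". In Table 3 that outcome is one of three in the delivery care utilisation domain, and the analysis text reserves no test, contrast or decision rule for it.
- **Claim (Discussion).** "By accounting for multiple inferences, we deal with the risk of specifying many outcomes".

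**The concern.** The Empirical analysis section itself warns about picking out chance findings from many tests and about type I error growing with the number of tests. That reasoning applies to 14 domain indices as much as to the items within one domain, and to two contrasts as much as to one. The stated procedures do not reach that level.

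Three consequences follow. A reader who takes the Discussion at its word would give an isolated significant domain more weight than it has earned. With neither contrast primary, emphasis can settle on one after the results are seen. The outcome that justified the sample size has no confirmatory test of its own, while an effect on any one of an unspecified set of outcomes is enough to open subgroup analyses.

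**Working it through.** **1. Reproduce the plan's figure.** The inputs, from Sample size calculations, are "an observed institutional delivery rate of 50 % at baseline [10] and an assumed coefficient of variation of 0.2"; 60 clusters per arm with 20 women per cluster; 80% power; and a difference of 8 points "compared with the control at 5 % level of significance". I use the unmatched cluster formula of Hayes and Bennett, two-sided:

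c = 1 + (1.96 + 0.842)² × [p0(1−p0)/m + p1(1−p1)/m + k²(p0² + p1²)] / (p1−p0)²

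With p0 = 0.50, p1 = 0.58, m = 20 and k = 0.2, the bracket is 0.0125 + 0.01218 + 0.04 × (0.25 + 0.3364) = 0.04814. Then c = 1 + 7.849 × 0.04814 / 0.0064 = 60.03 clusters per arm. The stated 60 reproduces, with power 80.0%. The stated power therefore belongs to a single unadjusted 5% test.

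**2. Count the family.** Domains: 3 (Table 2) + 6 (Table 3) + 5 (Table 4) = 14. Outcomes: 16 + 30 + 13 = 59, as the article states.

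**3. One contrast, no true effect.** Assume each domain index is judged at 5%; the article gives 5% only for sample size. The expected number of false-positive indices is 14 × 0.05 = 0.7, whatever the correlation. With independent domains the chance of at least one is 1 − 0.95^14 = 51.2%.

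**4. Two contrasts.** They share Groups A and C. With three equal arms of unit variance, A − (B+C)/2 has variance 1.5, A − C has variance 2, and their covariance is 1.5. The correlation is 1.5/√(1.5 × 2) = 0.866. By simulation, the chance that at least one of the two is significant in a given domain is then about 7.3%, against 1 − 0.95² = 9.75% for independent tests.

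**5. Correlated domains.** The domains are measured in the same women, so positive correlation is plausible, but the article gives no value. A simulation of 400,000 replicates, with 14 domains, equal arms and an assumed common between-domain correlation, gives the chance of at least one false-positive index:

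| Assumed correlation | One contrast | Both contrasts |
|---|---|---|
| 0 | 51% | 65% |
| 0.1 | 50% | 64% |
| 0.3 | 44% | 57% |
| 0.5 | 35% | 47% |
| 0.7 | 25% | 34% |

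The simulation uses simple contrasts of arm means in place of the difference-in-difference estimates.

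**6. Power for facility birth under within-domain adjustment.** The planned non-centrality is about 2.80. A Bonferroni correction for three items uses 0.05/3, with critical value 2.394, so power is Φ(2.80 − 2.394) = about 66%. That is the worst case. Step-down resampling that uses the correlation between items gives a value between 66% and 80%.

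**The case against.** Several points on the other side stand.

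- **Domain-wise families are a legitimate, pre-specified choice.** Nothing is wrong with the method inside a domain. The difficulty is that the Discussion's claim is wider than that choice supports.
- **No threshold or overall success rule is stated.** The article says that indices and adjusted p values are presented; it does not say that one significant domain would make the programme effective. The percentages above depend on the 5% assumption.
- **Further detail may exist.** The article refers to Additional file 4 for the empirical strategy, and that file is not shown. It may rank the contrasts or reserve a primary test, and leaving such detail there is no fault in itself. What remains is the mismatch between the procedures, the subgroup trigger and the protection claim, all of which the article does state.

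Some stronger readings are tempting but not supported.

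- A reader might compute 1 − 0.95^28 = 76% for two contrasts. That treats the contrasts as independent, whereas they share Groups A and C.
- A reader might take 51% as a minimum, or conclude that a false-positive domain is always more likely than not. With correlated domains, one contrast is at about 50% or below from a correlation of 0.1, and two contrasts fall below one half somewhere between 0.3 and 0.5.
- A reader might say that power for facility birth falls to 66%. That is the Bonferroni limit, not the planned step-down method. The 80% itself describes an endline comparison; the article expects the full analysis, with covariates and two rounds, to detect smaller differences.
- A reader might count the one-item family planning domain as a separate defect. A single test has nothing to correct within its domain, and it is already among the 14.
- How often chance alone would open the subgroup analyses cannot be derived, because *main outcomes* is undefined.

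**Conclusion.** The point holds as a mismatch between claim and procedure. Error control is described only within domains; 14 indices are tested in two overlapping contrasts with neither primary; the outcome that sized the study has no designated test; and the subgroup condition is undefined. The Discussion therefore overstates the protection.

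Under the 5% assumption, equal arms and between-domain correlations from 0 to 0.7, the chance of at least one false-positive domain index runs from about 51% down to 25% in one contrast and from about 65% down to 34% across both. Every value is at least about five times 5%, so the conclusion does not hinge on the correlation chosen. Power for facility birth under the within-domain adjustment lies between about 66% and 80%, not necessarily at the stated 80%. The change should be made, though it does not invalidate the design.

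**What to change.** Before the second-round data are analysed:

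1. Name facility birth, in one named contrast, as the single primary test at 5% without adjustment. The sample-size calculation then refers to a test that will be reported. Label the other contrast supportive.
2. Define *main outcomes*. Open subgroup analyses only on the primary result or on a multiplicity-adjusted result, and carry them out as interaction tests.
3. Keep the within-domain Westfall-Young p values. Then either report p values for the 14 domain indices adjusted across domains (Holm or step-down resampling) alongside them, or narrow the Discussion claim to control within each domain.

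The cost is analysis-plan wording, with no change to data collection. If the cross-domain adjustment is used, individual domain claims lose some power. As a worst-case illustration, a single test with the planned 80% power would have about 46% at 0.05/14, which is also a reason to keep the primary test outside that family. Narrowing the claim avoids this loss but leaves domain findings without study-wide error control, and the report should then say so.

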### Process evaluation

The process evaluation is intended to complement the impact evaluation. Indeed, it will run in parallel and draw on some of the same data sources. We will develop and critically assess a logic model of the project, mapping the pathways and intended effects of each component. We will next describe how the social franchise model evolves and the extent to which various components of the project are implemented on the ground. The process evaluation will then examine the factors that influence private providers’ decision to join the social franchise network. Finally, it will seek to understand how, if at all, the project influenced household decisions about healthcare and the behaviour of health providers.

Quantitative process measures will be collected to understand the extent of implementation, fidelity and scale (Table 5). These will focus on a number of different dimensions of implementation that map closely onto the various components within the project: uptake of social franchising; training of the health providers; information, branding and advertising; interactions with health workers in the social franchise network; and monitoring and feedback on quality and standards.

**Table 5 Tab5:** Process measures

Indicator	Survey tool
1. Uptake of social franchising	
Proportion of private health providers who join network (%)	Health provider census
Proportion of providers who left network in past year (%)	Health provider survey
Proportion of providers purchasing and selling SkyMeds (%)	Health provider survey
2. Training	
Proportion of social franchisees that have received clinical training (%)	Health provider survey
Proportion of social franchisees that have received training in use of technology (%)	Health provider survey
3. Information and marketing	
Proportion of women who have ever heard of Sky social franchise network (%)	Household survey
Proportion of social franchisees that have been branded (%)	Health provider survey
4. Contacts with health workers	
Proportion of women who had any contact with ASHAs during pregnancy (%)	Household survey
Proportion of individuals who have used telemedicine in past 6 months (%)	Household survey
5. Monitoring and feedback	
Proportion of social franchisees that have received supervision visits past 6 months (%)	Health provider survey
Proportion of social franchisees that have received feedback on quality past 6 months (%)	Health provider survey

Qualitative data collection will focus on understanding the process of implementation and how the social franchise model leads to impact. A 6-month period of intensive data collection using ethnographic methods will provide insight into the impact of the social franchise model on the dynamics of health care provision and health seeking behaviour at the village level and provide an important understanding of the context in which the intervention operates [38, 39]. The ethnographic work will seek to understand the intervention as implemented on the ground, the factors influencing providers’ decisions to join the franchise, the influence of the intervention on provider behaviour and stakeholder perceptions of the various providers and components involved in the Sky social franchise. As the ethnographic research process progresses, new hypotheses and questions will develop as new insights occur with increasing familiarity with the context [40]. Participant observation will be carried out by experienced anthropologists who speak the local language. Researchers will keep detailed field notes of informal observations and everyday conversations. If an informant provides more detailed information or partakes in a long discussion, the field worker will ask to digitally record the interview. Field notes and audio recordings of discussions will be transcribed in the original language and then translated.

The sample of villages selected will be a convenience sample informed by the results of the first round of quantitative data collection and drawn from the 60 clusters with a social franchise provider. The ethnographic research will take place in three broad locations, covering the catchment area of SkyHealth providers and their nearby SkyCare providers. Field notes will be double coded by the ethnographers. Preliminary findings and reflections from the ethnographic research will be fed back to the research participants through community meetings in each of the localities as a form of validation.

The second level of qualitative process evaluation will take place through repeat in-depth interviews. A document review and in-depth interviews with franchisor staff will be used to understand the process of implementation as well as the development of the project. Two rounds of interviews will take place with 10 members of staff at various levels in the organisations. In-depth interviews with senior staff will include topics and questions that facilitate understanding of the decision-making behind the intervention and the key factors that shaped its design. Interviews with field staff will include questions about the experience of implementation, the process of engaging with providers and adaptations to the project over time. A context record, which documents information that may impact the implementation, the mechanisms of change and the outcomes under measurement, will be developed. This exercise will be undertaken every 6 months, using short interviews to gather information about any developments, events, setbacks and news that may have impacted implementation of the project.

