### Study design

The impact study is designed as a prospective controlled before and after study in which the comparison group comprises matched areas both within the intervention districts and in neighbouring districts where social franchising is not introduced. The overall design is shown in Fig. 1. The primary sampling unit for much of the data collection is a cluster, defined as a ward (urban) or a village (rural) according to the most recent census. The impact evaluation involves the selection of study clusters to form three arms. Group A contains clusters with a social franchisee in the three intervention districts. Group B comprises clusters with no social franchisee in the same three districts. Group C is taken from neighbouring districts that do not have any social franchise network operating within them.

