**Fig. 1 Fig1:**
[figure not shown]
Study design and data collection

The selection of study areas was done 14 months after the first health providers were contracted at which time there were 50 SkyHealth and 343 SkyCare providers in the social franchise network. The selection of study clusters proceeds according to the following steps. First, we link every social franchisee to the census area in which it is located and select, at random, 60 intervention clusters (Group A). Second, we select similar controls by matching without replacement the intervention clusters to 60 comparison areas within the same three districts (Group B) [27]. As can be seen in Fig. 2, we impose a buffer zone of 0.5 km around intervention clusters to limit problems of contamination. We perform exact matching on district and urban residences and then within each strata, select pairs of clusters (nearest neighbour) with the smallest distance based on a Mahalanobis metric that is computed using census data on total population, % under 6 years, % females under 6 years, % literate females, % scheduled tribe, % scheduled caste, % cultivator and % “other” workers. Finally, we perform the same matching procedure to select 60 comparison areas in neighbouring districts (Group C).

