The health provider survey is administered at the same time as the household survey within the same communities. The sampling frame is generated from a census of all health providers within the study clusters conducted 1 month prior to the health provider survey. The census records the type of health provider and its geographic coordinates. For the purposes of the census, we define a health provider as any institution or individual whose primary purpose is to provide healthcare. We exclude drug sellers. Using this list, we randomly select for interview one private health provider (social franchisee in intervention clusters), one government health provider and one accredited social health activist in each cluster. The health provider survey tool includes the following modules: (1) health facility characteristics, (2) key health worker characteristics, (3) reproductive, maternal and newborn services, (4) maternal health knowledge, (5) maternal health practice, (6) motivation, (7) social franchise and business practices, and (8) experience of social franchise network.

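### The network exit rate in Table 5 comes from a survey that, in intervention clusters, interviews a social franchisee, so most leavers fall outside the sample and the rate is biased towards zero

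*Protocol article*

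**What the plan says.** In the Process evaluation section, Table 5, under uptake of social franchising, one row is "Proportion of providers who left network in past year". Its survey tool is given as "Health provider survey". The row above it, on the share of private providers who join, is assigned to the health provider census instead, so sources were chosen row by row. The exit row states no denominator.

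The Data collection section says whom the survey reaches in each cluster: "we randomly select for interview one private health provider (social franchisee in intervention clusters), one government health provider and one accredited social health activist". On the frame it says: "The sampling frame is generated from a census of all health providers within the study clusters conducted 1 month prior to the health provider survey".

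Under Study design, the arms are defined. "Group A contains clusters with a social franchisee in the three intervention districts". Group B clusters had no franchisee when selected, and Group C lies in districts where the network does not operate.

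The article uses the franchisor's administrative data, triangulated with the provider survey, to date the introduction of franchising in each cluster. It does not say that these data feed the exit row.

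**The concern.** An exit rate needs a group of members at a starting point and a count of those who have gone by the end. Here the private-provider interview in Group A is restricted to franchisees at about the time of interview. Being still in the network is close to a condition of entry, and the indicator asks how many are not.

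The second study objective is to understand the scale of the network and how far the programme is implemented. This is the only row in Table 5 on leaving the network. An exit rate that is too low would make the network look more stable than it is. It would also make it harder to tell whether a weak impact result reflects a model that did not work or providers who did not stay. That second point is about interpreting the impact estimate, not about bias in it.

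**Working it through.** The article states no exit rate, so there is no figure to reproduce. The check has two parts: whether any planned interview can reach leavers, and how the bias behaves under assumed values.

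**Where a leaver could be interviewed**

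- *Group A, private-provider interview (60 clusters, so about 60 interviews a round).* Restricted to a social franchisee. A provider who left during the past year is not eligible unless it is still recorded as a member, has rejoined, or is drawn because no franchisee remains in the cluster.
- *Group A, entry of clusters.* Every franchisee was linked to its census area and the 60 clusters were drawn from those areas. An area whose only franchisee had already left could not enter.
- *Group B.* No franchisee at selection. Leavers could appear only if the network later enters the cluster and a provider then leaves.
- *Group C.* No network in the district, so no leavers are expected.
- *Government provider and ASHA interviews.* These cannot supply private providers who left.
- *Survey modules on the franchise and on experience of the network.* They can record an exit only from a provider who is sampled.

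No planned interview is therefore aimed at leavers, and the routes that remain are incidental.

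**Direction and behaviour of the bias**

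Let d be the true share of the past year's members who left, and r a leaver's chance of interview relative to that of a current franchisee. Both are assumptions; neither is in the article. Then

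observed rate = d × r / (d × r + 1 − d)

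Example: d = 0.20 and r = 0.25 give 0.05 / (0.05 + 0.80) = 0.059.

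| True rate d | r = 0 | r = 0.1 | r = 0.25 | r = 0.5 | r = 1 |
|---|---|---|---|---|---|
| 10% | 0% | 1.1% | 2.7% | 5.3% | 10% |
| 20% | 0% | 2.4% | 5.9% | 11.1% | 20% |
| 30% | 0% | 4.1% | 9.7% | 17.6% | 30% |
| 40% | 0% | 6.3% | 14.3% | 25.0% | 40% |

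For every r below 1 the observed rate is below the true rate. Only r = 1, where leavers and stayers are equally likely to be interviewed, returns the true rate.

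**One concrete case**

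Assume one franchisee per Group A cluster, three private providers per cluster, and a random private provider interviewed wherever the franchisee has left. A leaver is then drawn with probability 1/3. Over 12 months, 60 members with true exit of 10%, 20% or 30% give 6, 12 or 18 leavers, of whom about 2, 4 or 6 are interviewed. The observed rates are 2/(2 + 54) = 3.6%, 4/(4 + 48) = 7.7% and 6/(6 + 42) = 12.5%. Leavers are recorded, but the rate is still less than half the true one.

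**The case against.** The best defence is that the article does not settle how round 2 is sampled. It calls the household survey a repeated cross-section but does not say this of the provider survey. If the franchisees interviewed in round 1 are re-interviewed in round 2, leavers among them are captured. Nor does the article say whether franchisee status at sampling comes from the provider census or from the franchisor's list; a listed provider who reports having left would be counted. These points stand, and they rule out any claim about the exact size of the bias. They do not remove the point, because the article describes selection from a census-based list and mentions neither re-interview nor a sample of former members.

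A reader might infer that the survey must record no leavers at all, or that the network would look stable whatever happened. The documents do not support that. The incidental routes listed above exist. The census row on joining might also show net shrinkage if the census is repeated, and the franchisor interviews, document review and six-monthly context record could reveal exits qualitatively.

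A reader might also extend the point to the rows on training, branding, supervision and feedback. Those rows are defined as proportions of social franchisees, so sampling current franchisees matches their denominator. No stated link runs from the exit row to the costing or to the financial sustainability question.

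Finally, this is one of 11 descriptive process measures. That limits its weight but does not make the source suitable.

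**Conclusion.** The point holds in a limited form. The stated source and the stated sampling rule, taken together, do not deliver the indicator: providers who left are largely outside the sample, and the rate is biased towards zero. The direction follows from the two passages, provided that leavers are less likely to be interviewed than stayers. The size cannot be computed, because the true exit rate, the number of franchisees and private providers per cluster, and the round 2 procedure for providers are not given. The tabulated values are illustrations only.

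The consequence is confined to this one row and to what is concluded about retention under the second objective. The 59 household outcomes, the difference-in-difference model and the sample size do not use it. It is worth correcting, but it does not threaten the main result.

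**What to change.** Define the row on a cohort.

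- **Denominator:** all franchisees on the franchisor's list 12 months before round 2, which matches the past-year wording. Alternatively, use all those on the list at round 1 and state the interval, which is about 14 months from January 2015 to March 2016.
- **Numerator:** those in the denominator who are no longer in the network at round 2.
- **Source:** the franchisor's administrative data, checked against the provider census or by re-contacting the franchisees interviewed in round 1.

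If re-interview of round 1 franchisees is already intended, one sentence saying so, with the denominator, would largely settle the matter.

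The cost is a new source and denominator for one row of Table 5 and a small amount of record checking. The retention figure will probably look less favourable. The other franchisee rows need no change.
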